### Data and safety monitoring plan

A Data and Safety Monitoring Plan (DSMP) will be implemented to ensure integrity of the study data and the safety of participants in the study. The plan will include the groups that are responsible for monitoring, the frequency for monitoring, and the information that will be monitored. In addition, the plan will define and describe the process for handling protocol deviations. All NHLBI data and safety monitoring guidelines will be followed. The principal investigator will be responsible for the oversight of data and safety monitoring. All Research Assistants responsible for data collection will be trained by the lead research team. All Research Coordinators must be certified as proficient in all study procedures prior to collection of data.

In order to track patient data linked to Coach McLungs^SM^, individual’s electronic medical record (EMR) numbers will be linked to study ID numbers. Names of participants with linkage to the ID number will be kept in a password-protected file on our secure server; only study staff will have knowledge of the password. Furthermore, this information, any consent forms and other forms with identifying information will be kept in locked filing cabinets that are separate from storage of de-identified data files. Only the research team will have knowledge of both the de-identified and identifiable data. Backup copies of all electronic data files will be updated immediately following the entry of new data. The backed-up version of the data file will be kept in a separate location on the server to protect against loss or damage. Furthermore, the network server upon which data files will be stored is backed up nightly to provide additional protection against loss. The lead research team will conduct error checking and preliminary analyses of all data to ensure accuracy prior to formal data analysis.

There are no physical risks anticipated from participation in this study. Since routine data are collected from the EMR, the participant burden will be low. Participants may feel concerned that their regular care will be impacted based on their decision to participate or not participate. Potential participants will be assured that their care will not be impacted by their decision to participate or not to participate in the study, and that they may withdraw at any time with no penalty. Data collected in the study will not be shared with anyone outside of the research team. Any signed consent and assent documents will be stored in a separate locked filing cabinet from identifiers. Only authorized staff will be allowed to access physical or electronic records from the study. Passwords will be used to protect computers and electronic files used for the project. Any breach of confidentiality will be immediately reported to the IRB.

### Groups responsible for monitoring

The protocol, informed consent and assent documents, and other relevant materials (such as surveys) will be reviewed and approved by the Atrium Health IRB. The IRB will be responsible for providing ethical oversight throughout the duration of the study, data analysis, and dissemination. Protocol deviations will be reported to the IRB according to IRB guidelines and the DSMP. All members of the study team will be involved in procedures to ensure subject safety and data integrity. All study personnel will receive training in human subjects’ protection and HIPAA, as well as study specific training on the protocol, procedures for maintaining data integrity and subject safety, applicable IRB policies, and on maintaining confidentiality of records.

Given the minimal risk associated with the intervention, we will utilize a data safety and monitoring board (DSMB) comprised of the lead research team. We will add one external non-study board member. The DSMB will meet annually to assess progress, preliminary data, and adverse events. Recommendations regarding the progress of the study will be documented for the study team, and potential concerns regarding the conduct of the study will be reported to the IRB or the Office of Clinical and Translational Research at Atrium Health.

### Monitoring study progress and subject safety

The study team will meet weekly or biweekly to review the progress of the study and any safety concerns. Information to be reviewed will include: (1) changes to the study protocol; (2) screening and enrollment log; (3) protocol violations; (4) reports submitted to the IRB. More frequent meetings may be required to address participant safety concerns. All reporting of protocol deviations will occur according to IRB requirements.

## Discussion

### Anticipated outcomes

All practices (100%) will receive a lunch-and-learn training on SDM communication and implementation of Coach McLungs^SM^. We assume 70% of patients and providers will begin adopting the intervention Coach McLungs^SM^. We expect that 50% of patients and providers patients will still be using Coach McLungs^SM^ by the end of the study.

Exacerbation outcomes will be measured over 18 months consisting of: ED visits, hospitalizations, and oral steroid prescriptions. We anticipate reductions in the proportion of intervention asthma patients with ED visits from 10 to 8%, patients with hospitalizations from 1.1% to 1.0%, with oral steroid prescriptions from 35 to 30%, and patients with a composite exacerbation outcome defined as having one or more of ED visits, hospitalizations, and patients with oral steroid prescriptions will decrease from 40 to 35%. Results of asthma outcomes for each practice will be presented to the practice at the 12-month post kick-off visit along with comparison aggregate data from the other implementation and control sites.

Safety oversight will be under the direction of a Data and Safety Monitoring Board. The DSMB will provide its input to National Institutes of Health staff.

Stakeholder engagement will prove valuable for identifying and addressing barriers to implementation, dissemination, and incorporation of results into practice. Ineffective communication [110, 111], low cultural competence [112], and lack of humility [113] are key barriers when working with vulnerable patients with low income, children, and minority groups [114–117].

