All outcomes and survey data will be collected and provided quarterly to the SAC in order to evaluate the implementation. Barriers and facilitators that emerge from 6-, 12-, and 18- month CFIR post-implementation surveys (see Additional files 3–5) will be reviewed by the SAC and feedback will be provided to the practices at 6-month follow up meetings.

Specific Aim 2: Conduct ongoing evaluation of patient-centered outcomes.

Based on a review of the implementation evaluation literature [61, 86, 87], the RE-AIM framework (Reach, Effectiveness, Adoption, Implementation, Maintenance) will be used for implementation evaluation. Reach, Maintenance: the number of patients and providers utilizing Coach McLungs^SM^ over time at each practice will be measured. As Coach McLungs^SM^ will be accessed through the EMR, we will be able to measure the number of times the intervention is delivered. Effectiveness: Patient health outcomes data of acute care visits for asthma exacerbations will be analyzed for patients who have a diagnosis of asthma (ICD-10 codes J45.0-J45.998) irrespective of intervention, allowing measurement of any outcome improvements over the life of the study. Data will be assessed at 6, 12 and 18 months for patient outcomes.

Specific Aim 3: Dissemination: Disseminate results and strategies for primary care implementation both locally and nationally. We will disseminate through local stakeholders, practice-based research networks, asthma advocacy national organizations, and academic research meetings for healthcare, primary care and asthma. We expect multiple methods, qualitative and quantitative results manuscripts in subsequent years (Fig. 1).

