### Sample size justification

We used a method to estimate sample size that takes into account the cluster randomization and the stepped-wedge design [88]. Our study design includes 21 clusters (facilities) with 6 time periods (including the baseline), 5 steps, 4 facilities switching from control to intervention at each step (except the third step will have 5), and an average of 30 patients per practice being continuously followed. Thirty patients is conservative as the typical number in a 6-month period is approximately 100. We conducted sample size analyses accounting for intracluster correlation (ρ = 0.20), individual autocorrelation (τ = 0.5), and cluster autocorrelation (π = 0.9) [88]. This design achieves 84% power to detect the hypothesized effect size difference of 10% in overall exacerbation between control (40%) and intervention (30%) periods (two-sided, α = 0.05). An effect size of 0.1 translates to a difference between groups of 10% absolute difference between intervention and control overall exacerbation rates.

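### The 84% power is for a 10-point difference between periods that the protocol ties neither to its own uptake assumption nor to the 5-point fall it anticipates

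*Protocol article*

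**What the plan says.** **Power.** Protocol article, Sample size justification: "This design achieves 84% power to detect the hypothesized effect size difference of 10% in overall exacerbation", the rates being "control (40%) and intervention (30%) periods (two-sided, α = 0.05". The same section describes the effect as a "10% absolute difference between intervention and control overall exacerbation rates". It takes 30 patients per practice, calls this conservative against a typical figure of about 100 in six months, and does not mention uptake.

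**Analysis population.** Under Aims and anticipated outcomes, Specific Aim 2, effectiveness is assessed in "patients who have a diagnosis of asthma (ICD-10 codes J45.0-J45.998) irrespective of intervention". The Study design section lets providers judge that some patients do not need the tool. The Analysis of outcomes section tests the intervention fixed effect, so non-users seen in intervention periods are part of the contrast.

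**Uptake and expected effect.** Discussion, Anticipated outcomes: "We assume 70% of patients and providers will begin adopting" the tool, and "We expect that 50% of patients and providers patients will still be using" it at the end of the study. The same subsection expects the composite exacerbation outcome to fall from 40% to 35%.

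**The concern.** The article fixes four things: the powered difference, the population, the uptake and the anticipated effect. It does not connect them. When 30% of patients never start and non-users stay in the analysis, an effect in users and a difference between periods are different quantities. A reader cannot tell which of them the 10 points is. Neither reading fits the Discussion, which anticipates half the powered fall.

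The stake is the interpretation of a null result. Read against 84% power, it would count as evidence that the tool does not work. If the all-patients difference that the team really expects is 5 to 7 points, a null result could be quite likely even when the tool works as hoped.

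**Working it through.** **Inputs from the Sample size justification.** There are 21 practices and 6 periods with the baseline counted; the numbers crossing over at the five steps are 4, 4, 5, 4 and 4. Patients per practice-period m = 30, or about 100 as the typical number. ICC ρ = 0.20, cluster autocorrelation π = 0.9, patient autocorrelation τ = 0.5. Two-sided α = 0.05.

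**Inputs from Anticipated outcomes.** Uptake of 70% at the start and 50% in use at the end; composite 40% to 35%.

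**Assumptions of this check.** Outcome variance is p(1−p) at the midpoint p = 0.35, that is 0.35 × 0.65 = 0.2275. The test uses a normal reference. τ is run at 0 and at 0.5.

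**Method.** Generalised least squares on practice-period means with fixed period effects:
- variance shared across periods = 0.2275 × [ρπ + (1−ρ)τ/m]
- variance specific to a period = 0.2275 × [ρ(1−π) + (1−ρ)(1−τ)/m]
- power = Φ(d/SE − 1.96)

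For m = 30 and τ = 0 the components are 0.2275 × 0.18 = 0.0410 and 0.2275 × (0.02 + 0.8/30) = 0.0106, giving SE = 0.0326. For m = 30 and τ = 0.5 they are 0.0440 and 0.0076, giving SE = 0.0277. For m = 100 the SE is 0.0254 (τ = 0) and 0.0235 (τ = 0.5).

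**The plan's own figure first.** For d = 0.10 and m = 30, power is Φ(0.10/0.0326 − 1.96) = 87% with τ = 0 and 95% with τ = 0.5. So 84% is not reproduced from the full set of stated inputs. It is approached when τ is left out: 83% to 87% for variances from 0.25 down to 0.225. That departure is conservative and is not the point here, but it is why τ is shown as a range.

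**Reading A: the 10 points is already net of uptake.** The stated power is then unaffected. If non-users gain nothing, the implied effect in users is 10/0.70 = 14.3 points. Taking 50% as an extreme lower bound, it is 10/0.50 = 20 points. From 40%, users would fall to about 26% or 20%. The protocol states no effect of that size.

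**Reading B: the 10 points is an effect in users.** With no gain in non-users, the all-patients difference is 10 × 0.70 = 7 points, or 10 × 0.50 = 5 points at the extreme.

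| All-patients difference | m = 30, τ = 0 | m = 30, τ = 0.5 | m = 100, τ = 0 | m = 100, τ = 0.5 |
|---|---|---|---|---|
| 10 points | 87% | 95% | 98% | 99% |
| 7 points | 57% | 72% | 79% | 85% |
| 5 points | 34% | 44% | 50% | 57% |

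A cross-check that does not depend on this variance model: 84% for 10 points implies SE = 0.10/(1.960 + 0.994) = 0.0338. With that SE, power is 54% at 7 points and 31% at 5 points.

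**The Discussion's own effect.** A fall from 40% to 35% is 5 points. If it is the difference between periods, the last row applies directly: 34–44% at m = 30, with no assumption about dilution (the variance is kept at 0.2275).

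**The case against.** The tempting stronger reading is that uptake of 70% falling to 50% shows the 84% power is not delivered. The documents do not support that, for four reasons.

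- The sample size section describes a contrast of overall rates between periods. Such a contrast already includes non-users, so multiplying it by uptake needs a further premise, that 10 points is the effect in users. The article does not state this. The objection stands in full.
- The 50% describes use at the end of the study. It is neither average uptake nor the share ever exposed, and a patient who stops using the tool need not lose its benefit. It can serve only as an extreme bound.
- Non-users may benefit. Rollout includes practice-wide training in shared decision communication, asthma guidelines and inhaler use. Providers may also leave out patients they judge not to need the tool, so non-users may be at lower risk. Scaling by headcount could then overstate the loss.
- At 70% uptake, 100 patients per practice-period and τ = 0.5, power is about 84.5%, which matches the stated figure.

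A reader might also infer that the 5-point fall is itself an effect in users and should be diluted again. The Discussion refers to intervention patients without defining them as users, so this does not follow either.

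It can further be said that the derivation of the 10 points may sit in the full protocol. That may be so. But the conflict between 30% and 35% in the intervention condition is inside the article, and a derivation elsewhere would not remove it.

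**Conclusion.** The point holds in limited form. The 84% is attached to a difference whose relation to uptake is not stated, and no figure in the article supports 10 points across all patients under the plan's own uptake. That would need about 14 points in users at 70% uptake, up to 20 at the extreme, while the article anticipates 5.

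If the 10 points is an effect in users, power at 70% uptake is about 57–72% at 30 patients per practice-period and 79–85% at 100. At the 50% extreme it is 34–44% and 50–57%. The part that needs no dilution assumption is that the anticipated 5-point fall has 34–44% power at 30.

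These figures rest on no benefit in non-users (for the diluted values only), variance at p = 0.35, a normal reference and τ between 0 and 0.5. They do not show that the stated power is wrong for a true 10-point difference between periods.

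**What to change.** Keep the analysis of all asthma patients by randomised step, and do not recover power by restricting it to users. In the Sample size justification:

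1. Define the target as the all-patients difference between control and intervention periods after expected uptake.
2. Reconcile that target with the fall from 40% to 35% in Anticipated outcomes, so that one composite effect appears throughout.
3. Restate the power for that difference at 30 and at about 100 patients per practice-period.
4. Give the effect in users that the target implies, and state what is assumed about benefit in non-users.

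The cost is a rerun of the power calculation and a few sentences. No extra patients or data are needed. The drawback is that the stated power will probably look less favourable.

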### Anticipated barriers and potential solutions

Problems with practice recruitment: As previously mentioned (Sub Aim 1.2), we have a strong record of practice collaboration utilizing healthcare system provider champions who support practice recruitment, implementation, and practice-feedback. By using a tailored approach [99], we hope to fully and effectively implement Coach McLungs^SM^ at 21 practices from a designated selection of ~ 75 practices available for recruitment within a large healthcare system. As previously discussed, a flexible implementation approach includes having a 9-month time window for practice recruitment; adapting the intervention for practice staff and provider preferences; other logistics such as rollout details, additional education needs, and adapting individual practice work flow logistics for use of Coach McLungs^SM^.

Problems with low provider engagement: Providers will be offered support with any potential barriers to using Coach McLungs^SM^. Additionally, during practice feedback, average Coach McLungs^SM^ enrollment numbers will be presented along with comparisons of aggregate data from all 21 practices to allow further discussion of practice or provider specific barriers.

Problems with low survey response: Provider surveys are designed using CFIR constructs to ask no more than 10 relevant questions taking ~ 5 min. Based on this approach our ED project obtained 100% return of pre-implementation ED surveys.

In summary, through previous experience with practice implementation across multiple healthcare settings, and extensive work with provider and patient partners and key stakeholders in the design and preparation for this implementation study, we anticipate overcoming barriers by responsively tailoring the implementation of Coach McLungs^SM^ to the needs of providers and culture of each practice. Understanding best practices for implementation and measuring patient-centered outcomes, such as changes in ED visits and hospitalizations, will inform the clinical and health services research communities with a goal to effect change in both healthcare delivery and health outcomes.

## Data Availability

Not applicable.

## Abbreviations

ED: Emergency department
SDM: Shared decision making
IT: Information technology
EMR: Electronic medical record
